**Figure 1. F1:**
[figure not shown]
RCT CONSORT flowchart. CONSORT: Consolidated Standards of Reporting Trials; eHEALS: Electronic Health Literacy Scale; IPAQ-SF: International Physical Activity Questionnaire—Short Form; PHQ-9: Patient Health Questionnaire-9; RCT: randomized controlled trial; WISQOL: Wisconsin Stone Quality of Life Questionnaire.

**Figure 2. F2:**
[figure not shown]
Study design table. MARS: Mobile App Rating Scale; WAFIR: WeChat-Based Applet Fluid Intake Reminder.

### Characteristics of Participants

The study is open to individuals aged 18 years or older, diagnosed with UC and admitted to Shekou Free Trade Zone Hospital (a tertiary general hospital) for urinary stone surgery, to participate. Eligible patients will be enrolled prior to discharge, either by a nephrologist or a urologist (Textbox 1).

Textbox 1.Inclusion, exclusion, and withdrawal criteria for participants’ recruitment.
**Inclusion criteria**
With a history of urinary calculi and having received urolithiasis surgery before.24-hour fluid intake <2500 mL.Age ≥18 years.Able to use WeChat daily.Able to read and write informed consent.
**Exclusion criteria**
Participants with obstructive uropathy, chronic urosepsis, renal failure, and renal tubular acidosis.Participants with congestive heart failure, psychiatric conditions, pregnancy, and primary hyperparathyroidism.Participants experienced complicated urolithiasis surgery (surgical procedures for urolithiasis that involve complex interventions, often requiring multiple operations during the follow-up period due to factors such as large stone burden, anatomical abnormalities, or postoperative complications, eg, percutaneous nephrolithotomy with residual stones or ureteroscopy requiring reintervention).History of recurrent urinary tract infection (>3 per year).Medication use increases stone risk.Participants with physical disabilities.
**Withdrawal criteria**
Participants will be deemed to have withdrawn from the study upon the voluntary withdrawal of their consent or if they fail to return a postintervention assessment within 30 days after the end of the intervention phase. All instances of withdrawal and the discontinuation of any participant’s involvement in the trial are meticulously documented.

### Intervention

#### Standard Care

Participants will receive standard dietary and regular recommendations, including an education profile and counseling to achieve a water intake and urine output ≥2500 mL, along with verbal health education counseling regarding urological calculi prevention during hospitalization and guidance on adequate hydration at discharge. A fixed-capacity water bottle will be provided. Phone calls will be given at each follow-up phase to reinforce the educational content and collect primary and secondary data through questionnaires.

#### WAFIR Intervention

Participants will receive the standard dietary counseling and an educational handout. The WAFIR will be introduced to the intervention group to enhance adherence to fluid intake and facilitate self-monitoring for the prevention of UC. The WAFIR will include features such as fluid intake reminders, fluid and urine value recording, urine color tracking, and health education, as well as an interactive group for communication among postoperative patients with urinary stones. The WAFIR will deliver personalized daily notifications to remind participants of increasing fluid intake exceeding 2500 mL. Additional educational content highlighting the benefits of adherence will be provided to the experimental group through the applet as well. Phone calls will be given at each follow-up phase to collect primary and secondary data via the questionnaires.

To address the limitations observed in existing mobile apps, we are developing an innovative WAFIR aimed at improving participants’ adherence to fluid intake and reducing the recurrence of UC. This intervention will incorporate multiple functionalities to enhance participants’ awareness and control over their fluid consumption. The WAFIR will consist of 4 main pages:

Homepage: The primary interface of the WAFIR provides a user-centric platform for monitoring and managing daily hydration objectives. It enables patients to set personalized fluid consumption targets, log daily fluid intake, record urine output volumes, and visually assess urine color to determine hydration status.Statistical Analysis page: This offers a comprehensive overview of patients’ hydration and urination patterns over multiple time frames. It presents historical data and trends in fluid intake and urine output, displayed on a daily, monthly, and annual basis. Through graphical visualizations, this module empowers patients and health care providers to monitor adherence trends, identify patterns, and adjust intervention strategies to optimize long-term compliance with fluid intake recommendations.Health Education Knowledge page: The evidence-based materials tailored to kidney stone prevention are provided, which include detailed information on various types of UC and targeted prevention strategies. This is delivered through accessible formats like articles.Function page: The applet will send notification messages at regular intervals, customized based on the patient’s daily habits. The notification module delivers customized reminders designed to promote consistent fluid intake. By sending timely and context-relevant messages, the system encourages adherence to prescribed hydration regimens, addressing barriers such as forgetfulness or situational constraints.

The development of the WAFIR will begin with its registration on the WeChat Official Accounts platform, initiating a structured 6-phase development process as depicted in Figure 3. The first phase, WAFIR requirement analysis, will involve a multidisciplinary team—including urological nurses, doctors, nursing education specialists, nutritionists, and postoperative patients with UC—to conduct needs assessments, define functional specifications (eg, fluid intake reminders and urine output tracking), and develop evidence-based content through stakeholders’ feedback. The second phase will be the WAFIR design phase, where a user-friendly interface and function module will be created in collaboration with software developers and health care providers. The third phase of the WAFIR feasibility assessment will evaluate the prototype’s technical performance and clinical utility through testing by the development team and clinical professionals. In the fourth phase, the WAFIR acceptability assessment will engage a cohort of 19 participants—comprising 3 urological nurses, 3 urological doctors, 2 nursing education nurses, 1 nutritionist, and 10 postoperative patients—to assess usability and collect feedback using validated tools such as the Mobile App Rating Scale [29] and the mHealth Evidence Reporting and Assessment checklist [30], ensuring that the WAFIR meets patient needs prior to the RCT. The fifth phase, monitoring and maintenance, will focus on ongoing improvements, incorporating user data and feedback to refine content and functionality. Finally, the clinical application phase will implement the fully validated WAFIR in real-world clinical settings for the RCT, aiming to enhance health management and prevention outcomes.

**Figure 3. F3:**
[figure not shown]
Development of WAFIR flowchart. eHEALS: Electronic Health Literacy Scale; IPAQ-SF: International Physical Activity Questionnaire—Short Form; PHQ-9: Patient Health Questionnaire-9; RCT: randomized controlled trial; WISQOL: Wisconsin Stone Quality of Life Questionnaire.

#### Intervention Mechanism

The mechanism of the WAFIR provides a robust and constructive framework by providing a feedback loop, which is depicted in Figure 4, to enhance the adherence awareness of fluid intake for patients with UC, which is applied following these processes: goal setting to define the objective and specify the desired outcome: clearly define the water intake goals for patients, such as the amount of drink to be consumed at designated times; begin by establishing long-term and short-term goals. The long-term goal could be to prevent further formation of UC, while a short-term goal could be to ensure a specific amount of water intake per day. Action planning outlines a detailed process on how to achieve the set goals. This could involve developing a WeChat applet monitoring system to track each patient’s water intake, deliver hydration reminders, formulate strategies to overcome barriers to hydration, provide educational documents, facilitate peer support from the community, and offer access to professional guidance. Essential training is also provided to ensure that patients are adept at using the WAFIR to manage and monitor their water intake. Self-monitoring of behavior: encourage patients to monitor their behavior, for instance, recording their daily water intake, the color of their urine, and the physical activity level they perform daily.

**Figure 4. F4:**
[figure not shown]
The mechanism of WAFIR. WAFIR: WeChat-Based Applet Fluid Intake Reminder.

Concurrently, educating patients on the importance of proper hydration and its significant impact on health increases their intrinsic motivation. Nurses assist patients with behavioral skills development by setting reminders, recording water intake, and developing strategies to overcome barriers to hydration. Behavior feedback: the WAFIR incorporates feedback mechanisms to provide real-time feedback to patients. This is using notifications, alerts, or visual indicators to signal when patients’ hydration goals are not met. Data collected through the WAFIR are analyzed to recognize patterns of compliance and noncompliance, which help regulate behavior and reduce disparities between current and desired behaviors. This fosters self-monitoring and self-regulation through the WAFIR to enhance patients’ sense of self-efficacy for their drink intake. Goal review: regularly review the goals in light of the monitored behavior and feedback, which may involve adjusting the frequency of reminders, fluid intake goals, physical activity levels, dietary habits, or health literacy to align with patient behavior and feedback. This approach is supported by Partridge et al [31], who demonstrated that mHealth interventions using techniques such as goal setting, self-monitoring of behavior, and feedback are more effective in promoting behavior modification than apps lacking these features. Similarly, a systematic review by Middelweerd et al [32] evaluated 41 apps in iTunes and 23 apps in Google Play, identifying goal setting, self-monitoring, and feedback on performance as common approaches to promote intention to behavioral alteration.

### Theory-Based Technique

Control theory examines how individuals monitor and modulate their behaviors to attain specific objectives. It underscores the importance of self-regulation, including behavior self-assessment, the establishment of targets, and the use of feedback mechanisms [33]. Within the domain of health behaviors, control theory delineates the strategic adjustment of behaviors to fulfill health-related goals. Meanwhile, control theory, which comprises an input function, a comparator with reference values, an output function, an effect on the environment or others, and disturbance, is majorly applied to bridge the intention-behavior gap in artificial intelligence (AI) for physical action change. The detailed diagram described in Figure 5 closely aligns with the WAFIR mechanism. The goal-setting and action-planning stages correspond to the input function and comparator phases; the self-monitoring of behavior and behavior feedback phases can be reflected in the output function; and the goal review stages can be found in the effects phase of the control theory, with disturbances identified accordingly.

**Figure 5. F5:**
[figure not shown]
Control theory diagram.

### Ethical Considerations

This study received ethics approval from the University of Hong Kong/Hospital Authority Hong Kong West Cluster Ethics Review Board (UW24-754) and the Qianhai Shekou Free Trade Zone Hospital Ethics Committee (2024-055(Shen)-01) in December 2024. Written informed consent will be obtained from all participants, ensuring their right to withdraw, per the Declaration of Helsinki. Participant data will be deidentified, stored securely, and accessed only by authorized personnel to ensure privacy and confidentiality. The trial does not involve physical harm. No compensation will be provided, with voluntary participation incentivized by potential health benefits. No identifiable images or information will be included in the manuscript or supplementary materials. All procedures adhere to institutional and international ethical standards.

### Trial Registration

Our trial was retrospectively registered on ClinicalTrials.gov (NCT06990672) on May 24, 2025, after the initiation of recruitment. This delay was unintentional and resulted from unforeseen administrative challenges, including delays in securing institutional registration and coordinating with the tertiary hospital’s research office in Mainland China, which were exacerbated by the rapid progression of the study timeline following the development of the WAFIR applet in February 2025. Recruitment commenced on March 1, 2025, and was completed by June 27, 2025, prior to registration, due to these logistical constraints. We affirm that this retrospective registration does not reflect an intent to bias reporting, as the study protocol, including design, outcomes, and intervention details, was finalized and documented internally before recruitment began, adhering to the original research plan.

### Outcome Measures

#### Primary Outcomes

##### 24-Hour Urine Volume

To initiate the 24-hour urine collection, upon waking in the morning, void into a graduated container and document the precise start time (eg, 8 AM). On the subsequent morning, near the 24-hour end point (eg, 8 AM), we record the urine volume once more. Throughout this period, we use platforms such as the WeChat applet or alternative recording methods to track and document the cumulative urine output.

##### 24-Hour Fluid Intake Volume

This measure is to calculate the participants’ fluid intake for a full 24-hour period. This comprehensive record should span a full 24-hour period, ideally starting and ending at the same time of day to standardize the assessment. Participants will be instructed to record the fluid consumed using either the WAFIR or another recording method, including water, tea, coffee, Chinese herbal tea, and other eligible liquids. The data on daily fluid consumption volume can be summarized automatically once patients log the data in the WAFIR in the intervention group. However, the participants must manually report the fluid intake volume in the control group. This is the direct parameter that reflects the adherence to fluid intake in the WAFIR.

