### Methods of Analysis

The study outcomes will be reported to adhere to the guidelines outlined in the CONSORT (Consolidated Standards of Reporting Trials) 2010 statements [44]. Statistical tests such as a 2-tailed *t* test and chi-square test will be used for continuous and categorical variables within 2 groups. The principal analysis will compare the fluid intake volume between the intervention and control groups using the 2-tailed *t* test. Secondary outcomes such as WISQOL, PHQ-9, and eHEALS will use repeated measures of ANOVA since they are measured over time and between 2 groups. If necessary, subgroup analyses will be conducted to explore whether the effect of the intervention varies across different demographic or clinical subgroups. Intention-to-treat analysis will be used to assess the impact of the treatment and its generalizability as well as the missing data. A planned interim analysis will be performed to evaluate both efficacy (whether the intervention shows sufficient benefit to potentially stop the trial early) and futility (whether the intervention is unlikely to demonstrate benefit if the trial continues) after 50% (74/148) of the target sample size have completed the primary end-point assessment. A significance level of *P*<.05 will be used to determine statistical significance, and all data analysis procedures will be conducted using the SPSS (version 26.0; IBM Corp) software package.

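### Fluid intake is summed by the applet in one arm and reported manually in the other, and no section says which record the principal t test uses

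*Protocol article*

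**What the plan says.** The section 24-Hour Fluid Intake Volume asks for a full 24-hour record but leaves the method open: "Participants will be instructed to record the fluid consumed using either the WAFIR or another recording method". It then separates the arms. For the intervention group, "The data on daily fluid consumption volume can be summarized automatically once patients log the data in the WAFIR in the intervention group". For the other arm, "However, the participants must manually report the fluid intake volume in the control group".

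24-Hour Urine Volume, the other primary outcome, uses a graduated container but is equally open on recording: "we use platforms such as the WeChat applet or alternative recording methods to track and document the cumulative urine output".

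Methods of Analysis states: "The principal analysis will compare the fluid intake volume between the intervention and control groups using the 2-tailed" *t* test.

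Other sections describe a route that could be common to both arms. Standard Care says: "Phone calls will be given at each follow-up phase to reinforce the educational content and collect primary and secondary data through questionnaires". WAFIR Intervention says: "Phone calls will be given at each follow-up phase to collect primary and secondary data via the questionnaires". Intervention Nurses has nurses collecting baseline, 1-month and 3-month data by questionnaire. The Abstract describes the trial as open-label, with WAFIR added to standard care.

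**The concern.** In one arm the applet is both the treatment and, on the face of the intake section, the recording tool. Intervention Mechanism lists self-monitoring, feedback and alerts about unmet goals as active parts of WAFIR. If the analysed intake comes from applet logs in one arm and manual reports in the other, the groups differ in two ways after randomisation: the treatment, and how a drink becomes a number. The principal test cannot tell the two apart. Randomisation and intention-to-treat do not help, because the difference arises after allocation. A larger sample does not help either, because it estimates the same mixed quantity more precisely. T0 precedes the intervention, so if the applet enters measurement only after T0, comparing change from baseline would not remove the shift.

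**Working it through.** **1. Which source feeds the test?**

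| Section | Intervention arm | Control arm |
|---|---|---|
| 24-Hour Fluid Intake Volume | logged in WAFIR, can be summed automatically | reported manually |
| 24-Hour Urine Volume | applet or alternative | applet or alternative, not split by arm |
| WAFIR Intervention / Standard Care | calls with questionnaires | calls with questionnaires |
| Intervention Nurses | questionnaires | questionnaires |
| Methods of Analysis | fluid intake volume, source not named | fluid intake volume, source not named |

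The only section that defines the intake outcome splits the method by arm. The calls and questionnaires could give a common value, but no section makes them the analysed source.

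**2. The plan's own figures.** Sample Size gives d = 0.61, alpha .05, power 0.80, 92 evaluable and 148 recruited at 38% attrition.
- A two-sided two-sample t test at these inputs needs 43.17, so 44 per arm, 88 in total.
- Dividing by 0.955 (the Wilcoxon-Mann-Whitney efficiency) gives 43.17/0.955 = 45.2, so 46 per arm, 92 in total, which matches.
- 92/(1 − 0.38) = 148.4, which supports 148.

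The gap between 88 and 92 is conservative and separate from this point. A common recording method leaves the sample size unchanged.

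**3. Scale of a possible shift.** The documents give no SD and no estimate of a method difference. Assume a shift of 250 mL and an SD of 500 to 800 mL:
- 250/800 = 0.31 SD, and 0.31/0.61 = 51% of the planned effect
- 250/500 = 0.50 SD, and 0.50/0.61 = 82% of the planned effect

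**4. Effect on the test over a range of shifts.** Let b be a pure measurement shift in SD units, with n per arm, equal SDs and approximately normal data. The t statistic then follows a noncentral t with 2n − 2 degrees of freedom and noncentrality b√(n/2). For b = 0.2 and n = 46, the noncentrality is 0.2 × √23 = 0.96. The mL column is b times 500 and 800.

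| b (SD) | mL | P(p<.05), no true effect, 46 per arm | Same, 74 per arm | Power at true d = 0.61 if the shift goes against WAFIR, 46 per arm |
|---|---|---|---|---|
| 0 | 0 | 5.0% | 5.0% | 82.5% |
| 0.1 | 50–80 | 7.6% | 9.3% | 67.7% |
| 0.2 | 100–160 | 15.8% | 22.7% | 49.4% |
| 0.3 | 150–240 | 29.6% | 44.2% | 31.3% |
| 0.4 | 200–320 | 47.5% | 67.6% | 16.9% |

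Every value of b is an assumption. The table shows how sensitive the test is to a shift. It does not show that one occurred.

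**5. Co-interventions.** Standard Care states: "A fixed-capacity water bottle will be provided. Phone calls will be given at each follow-up phase to reinforce the educational content". WAFIR Intervention mentions neither the bottle nor reinforcement by phone, while the Abstract says that arm also received standard care. These sections do not settle whether both items were given in both arms.

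**The case against.** The best defence is that the contrast is narrower than it first looks. Both arms self-record over 24 hours, and the stated difference lies in how entries are totalled and reported. Pre-visit reminders in Data Collection are not limited to one arm. Primary data are also gathered by call or questionnaire in both arms, so the analysed value may already come from one common route. Urine volume, measured in a graduated container, gives partial corroboration.

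Much of this stands. It limits the point to a possible difference in capture plus an unnamed source. It does not remove it, because the section defining the outcome assigns different methods by arm and no other section overrides it. Urine recording has the same applet-or-alternative wording. The Discussion covers interview quality and urine-collection accuracy, but not a method difference between arms.

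Several stronger readings are tempting but unsupported:
- **That logging inflates recorded intake in the WAFIR arm.** Nothing in the documents gives a direction. Prompted logging could capture more drinks, and incomplete logging could capture fewer. If only controls had a fixed-capacity bottle, that would be a measuring aid on their side.
- **That controls gave an unprompted recalled total.** The protocol asks for a full-day record from participants generally.
- **That the bottle was withheld from the WAFIR arm.** Silence in a condensed article is weak evidence, given the Abstract.
- **That dark urine is ascertained differently by arm.** The protocol gives no collection method for that secondary outcome.

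**Conclusion.** The point holds. As written, the principal comparison ties recording method to arm in an open-label trial whose treatment includes the recording tool, and the source of the analysed value is not fixed. The result would mix the treatment effect with any difference in capture.

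The size and direction are unknown. With no true effect, assumed shifts of 0.2 to 0.3 SD would give p<.05 in about 16% to 30% of trials at 46 per arm and 23% to 44% at 74 per arm. Shifts of the same size in the other direction would cut power at 46 per arm from 82.5% to between 49% and 31%. These figures rest on assumed shifts, equal SDs and approximate normality.

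A reader might infer that intake should now be demoted in favour of urine volume. The documents do not support that. Urine volume is already a primary outcome and may share the recording problem. Changing outcome priority after collection in a retrospectively registered trial would also be a post hoc change with its own cost.

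**What to change.** **Definition.** State that the analysed 24-hour intake and 24-hour urine volume each come from one identical record, taken the same way in both arms at T0, T1 and T2. Use WAFIR logs only to describe usage. The cost is a small extra recording burden for the WAFIR arm on the assessment days.

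**Where collection is already complete.** The Abstract and Results place it at or near its end in September to October 2025, so a new record is no longer possible for T0 and T1. Instead:
- Take the analysed value from the questionnaire or call source in both arms, if it was recorded. Check that WAFIR participants were not simply reading out the applet total, since the source would then be common in name only.
- Date this decision and say whether between-arm results had already been seen.
- Keep both primary outcomes as planned, and interpret intake alongside graduated-container urine volume.
- Name the source of the analysed value for each arm, and report any remaining method difference as a limitation.

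This needs a data check and a few sentences of text, and no change to the sample size.

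**Reconciliation.** Make the Abstract, Standard Care and WAFIR Intervention agree on whether the bottle and the education calls were given in both arms.
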